### Blinding

The primary outcome is assessed blindly. Follow-up data will be collected centrally by blinded assessors at the coordinating centre (Imperial College London).

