### Secondary outcomes

The secondary outcomes include:

Mortality rates in each group.Adverse events (AEs) related to the GCS (assessed at 7 days, in those enrolled in the intervention clusters only).QoL score at 7-days and 90-days postsurgical procedure assessed using the EuroQol-5 Dimension(EQ-5D).Resource use and costs of healthcare, and days off work and normal activities, up to 90 days.

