### Follow-up periods

Participants will be followed up at 7-days and 90-days postsurgical procedure. Follow-up data will be collected via telephone or online questionnaire (the link to the questionnaire will be sent via email or SMS).

At 7 days postsurgical procedure, data on self-reported VTE outcome will be collected and the EQ-5D will be administered. For those participants who were enrolled in the intervention cluster only (ie, sites which were randomised to issue GCS to short-stay surgical patients), information on AEs related to GCS will also be collected.

At 90-days postsurgical procedure, data on self-reported VTE outcome will be collected, together with the EQ-5D and information on the healthcare resource use.

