### Data collection and confidentiality

Participant data will be collected and entered onto the web-based database REDCap by the local research team. Data will be filed for 10 years as per local policy and then deleted. Data will be monitored by the trial manager for quality and completeness, and missing data will be requested from the participating sites, as per the data monitoring plan. The trial manager will only have access to pseudonymised data on REDCap.

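### Follow-up is declared blinded, but stocking adverse events are asked about in GCS clusters only, at the same central day-7 contact that records VTE, so a telephone assessor learns the arm

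*Protocol article*

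**What the plan says.** All references are to the protocol article.

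- **Trial design** and **Blinding** both claim blinded assessment of the primary outcome: "The primary outcome is assessed blindly". Blinding adds: "Follow-up data will be collected centrally by blinded assessors at the coordinating centre".
- **Follow-up periods** gives the mode of contact: "Follow-up data will be collected via telephone or online questionnaire". The day-7 content for everyone is: "At 7 days postsurgical procedure, data on self-reported VTE outcome will be collected and the EQ-5D will be administered". An arm-specific element follows: "For those participants who were enrolled in the intervention cluster only", "information on AEs related to GCS will also be collected". The day-90 content is self-reported VTE, EQ-5D and resource use, with no arm-specific item.
- **Secondary outcomes** repeats the restriction for GCS-related adverse events: "assessed at 7 days, in those enrolled in the intervention clusters only".
- **Data monitoring, safety and quality control** says these adverse events are gathered centrally at 7 days.
- **Recruitment and randomisation** makes the recruiting centre the unit of randomisation and has the Trust told its allocation by letter.
- **Data collection and confidentiality** says: "Participant data will be collected and entered onto the web-based database REDCap by the local research team".

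**The concern.** The day-7 contact has different content in the two arms. Someone conducting it by telephone has to know whether to ask about stockings, so the script discloses the allocation to the person described as blinded.

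Cluster allocation makes this worse than it would be in an individually randomised trial. There, an unblinding item reveals one participant's arm. Here, one call can reveal the arm of everyone from that site.

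Participants and site staff know the allocation, so the assessor is the only party for whom the article claims blinding. VTE is described as self-reported, and how an answer is probed and coded can affect whether an event is recorded. Few events are expected, so a modest difference in recording between arms could move the primary comparison. It could also affect the futility decision at 50% of mature data.

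**Working it through.** **1. The passages side by side**

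| Feature | Statement | Section |
|---|---|---|
| Who collects follow-up | Central assessors, blinded | Blinding |
| Day-7 VTE | Both arms | Follow-up periods |
| Day-7 GCS adverse events | Intervention clusters only | Follow-up periods; Secondary outcomes |
| Where those events are collected | Centrally, at 7 days | Data monitoring, safety and quality control |
| Day-90 items | Same in both arms | Follow-up periods |
| Unit of allocation | Centre | Recruitment and randomisation |

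The first four rows cannot all hold for a telephone contact in which one person asks all the items. The last two rows limit the reach. Nothing at day 90 reveals the arm by itself, so carry-over to day 90 requires that assessors can see the site and that the same or communicating staff handle both contacts. Asking about VTE first protects the first call to a site, but not later calls if the site is visible.

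**2. The plan's own sample size, as background**

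Inputs from Sample size and study duration: 1.0% vs 0.5%, 90% power, 5% significance (taken as two-sided), ICC 0.001, mean site size 350, coefficient of variation 0.25, 25 + 25 sites.

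- Two-proportion formula without clustering: 6,256 per arm.
- Design effect: 1 + ((1 + 0.25²) × 350 − 1) × 0.001 = 1 + 370.875 × 0.001 = 1.371.
- Total: 2 × 6,256 × 1.371 ≈ 17,152, close to the stated 17,500.
- 17,500 / 0.85 = 20,588, and 21,472 / 20,588 = 1.043, the implied group sequential inflation.

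The point does not depend on this figure. The check only confirms the basis for the illustration.

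**3. Illustration of sensitivity**

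Assumptions not in the article: the true rate is 1.0% in both arms, and one arm records a fraction r of its events.

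- Evaluable per arm: 17,500 / 2 = 8,750. Expected events per arm: 87.5.
- Effective n per arm: 8,750 / 1.370875 ≈ 6,383.
- With p₁ = 0.010, p₂ = 0.010r and p̄ their mean: SE₀ = √(2p̄(1 − p̄)/6,383) and SE₁ = √((p₁(1 − p₁) + p₂(1 − p₂))/6,383).
- Chance of a significant result: Φ((p₁ − p₂ − 1.96·SE₀)/SE₁) + Φ((−(p₁ − p₂) − 1.96·SE₀)/SE₁).

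Worked case, r = 0.9: both SEs are about 0.00172, and 0.001/0.00172 ≈ 0.58. The chance is Φ(0.58 − 1.96) + Φ(−0.58 − 1.96) ≈ 0.084 + 0.006 = 0.090.

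| Under-recording in one arm | Events not recorded | False-positive rate |
|---|---|---|
| none | 0 | 5.0% |
| 5% | about 4 | 6.0% |
| 10% | about 9 | 9.0% |
| 20% | about 17.5 | 22.3% |

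**4. What differential recording alone would need to reach significance**

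- At 1.0% vs 0.68%: SE 0.00162, and 1.96 × SE ≈ 0.0032. That is 0.0032 × 8,750 = 28 events, or 32% of one arm's events.
- At 0.50% vs 0.28%: SE about 0.0011, and 1.96 × SE ≈ 0.0022. That is about 19 events, or 44%.

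**The case against.** The best defence is that the conflict is narrow.

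- **Day 90.** The primary outcome runs to 90 days, and the day-90 contact has no arm-specific item. A reader might infer that every telephone follow-up is unblinded. The article does not support that: day 7 is affected directly, and day 90 only through carry-over whose conditions it does not state. This stands.
- **Online forms.** A self-completed form involves no assessor who asks or omits anything. This largely stands, although whoever sends or processes an arm-specific form could infer the arm. The split between telephone and online is not given.
- **Masked confirmation.** The statement that the primary outcome is assessed blindly might refer to separate masked confirmation of events in the full protocol, which is not shown. That is possible. It would protect classification of reported events, but not how they are elicited. It would also not make the statement about the staff collecting follow-up true.
- **Local data entry.** A reader might infer that unblinded site staff enter VTE outcomes. The sentence is general, the one in Blinding is specific to follow-up, and the natural reading is enrolment and procedure data. The two need reconciling in wording, but this is not evidence of unblinded outcome entry.
- **P values.** A reader might infer that tests are planned on a one-arm adverse-event outcome. The safety paragraph also covers serious adverse events and says only that any p values will be read descriptively, so this does not follow.
- **Size.** To produce significance in the expected result from recording alone, about 32% to 44% of one arm's events would have to go unrecorded. The article gives no evidence of that, and it calls the outcome objective. This stands against any claim that the primary result is biased.

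**Conclusion.** The concern holds in limited form. The article claims a property, blinded central collection of follow-up, that its described day-7 procedure does not deliver for telephone contacts. This is a contradiction between stated design features rather than detail left to a fuller document. Spread to other participants at a site, and to day 90, is plausible but conditional on assessors seeing site identity.

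No bias has been shown, and its size and direction are unknown. The figures of 9% and 22% describe sensitivity under an assumed true rate of 1.0% in both arms and assumed under-recording of 10% and 20% in one. At 5% under-recording the false-positive rate barely moves, to 6%. It would be wrong to conclude that the primary outcome is unblinded throughout. Correction is still warranted, because assessor blinding is the only blinding claimed and unblinded collection cannot be repaired at analysis.

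**What to change.** 1. Ask the same lower-limb and skin event questions at day 7 in both arms, worded without mention of stockings and placed after the VTE and EQ-5D items.
2. Hide site identity and allocation from the assessors' REDCap view. Item order alone does not protect later calls to a site whose arm is already known.
3. If this is not done, reword Trial design and Blinding so that they do not claim blinded collection at day 7.
4. In Data collection and confidentiality, limit local data entry to data other than follow-up, so that it agrees with Blinding.

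The cost is a few extra questionnaire items for control participants (about 21,472 / 2 = 10,736 people) and a database access setting. There are no extra visits, and the sample size does not change. The protection is partial: participants know whether they wore stockings and may say so on the telephone.

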### Follow-up periods

Participants will be followed up at 7-days and 90-days postsurgical procedure. Follow-up data will be collected via telephone or online questionnaire (the link to the questionnaire will be sent via email or SMS).

At 7 days postsurgical procedure, data on self-reported VTE outcome will be collected and the EQ-5D will be administered. For those participants who were enrolled in the intervention cluster only (ie, sites which were randomised to issue GCS to short-stay surgical patients), information on AEs related to GCS will also be collected.

At 90-days postsurgical procedure, data on self-reported VTE outcome will be collected, together with the EQ-5D and information on the healthcare resource use.

### Data collection and confidentiality

Participant data will be collected and entered onto the web-based database REDCap by the local research team. Data will be filed for 10 years as per local policy and then deleted. Data will be monitored by the trial manager for quality and completeness, and missing data will be requested from the participating sites, as per the data monitoring plan. The trial manager will only have access to pseudonymised data on REDCap.

### Statistical analysis

All statistical analyses will be governed by a comprehensive statistical analysis plan, authored by the study statisticians and agreed by the independent Trial Steering Committee (TSC).

The main analysis will be according to the intention-to-treat principle and will compare the rates of VTE at 90 days, measured at an individual level, using hierarchical (multilevel) logistic regression, adjusting for any other prespecified strongly prognostic individual baseline covariates and site-level baseline covariates, with site itself as a random effect. This will be performed independently by the Edinburgh Clinical Trials Unit who will have sole access to the final REDCap dataset. The findings will be assessed for robustness against any missing data, first using multiple imputation assuming this data are missing at random and, if appropriate and the data permit, further sensitivity analyses will be attempted under any plausible missing data mechanisms not missing at random. Secondary outcomes will be analysed in a similar fashion with generalised linear models appropriate to the distribution of the outcome. Safety data will be summarised descriptively.

### Internal pilot

There will be an internal pilot of feasibility at the end of 6 months of recruitment (beginning of month 7 to end of month 12 of the overall study timeline). We will start recruiting the (minimum) 50 sites at four sites per month. The 100% recruitment rate to meet the sample size is 20 participants per centre month (accounting for the staggered site set-up). This equates to a target of 1440 participants at the end of the 6-month internal pilot. A stringent criterion of <5% failure to receive allocated intervention is set as a marker of crossover between trial arms. Regarding follow-up, a marker of <15% lost to follow-up would be indicative of green progression. The amber criteria is set at 75%–99% of recruitment. This equates to a minimum of 1080 participants across the 6-month internal pilot period and an associated mean recruitment rate of 15 participants per centre month. We have set an amber criterion for site set-up independent of total recruitment number, hence, even if the total participant number is at 100%, if the number of sites set-up is <24 then this would stimulate a review of the site set-up strategy. Any amber criteria would prompt a review of the trial methodology and recruitment strategy. The red criteria, that is, consideration of stopping the trial early, is set at <75% recruitment and is equivalent to achieving fewer than 1080 participants across the 6-month internal pilot period. An independent threshold for site set-up has been set at <18 sites. The TSC will meet at the end of month 13 (allowing 1 month of processing time after the 6 months of recruitment) with blinded estimation of the rate of VTE for each arm. This will confirm the sample size or lead to a sample size re-estimation.

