### Sample size and study duration

Good quality data for the incidence of VTE in low VTE risk surgical patients not receiving thromboprophylaxis is lacking. Data from the recently published GAPS RCT on moderate and high risk patients reported 29 (1.6%)/1858 VTE events at 90 days.^11^ The VTE rate for short-stay procedures in individuals formally assessed as being at low risk of VTE would be expected to be lower than this, however, as these short-stay patients are not receiving a thromboprophylactic dose of LMWH, we have conservatively assumed an overall control (no stockings nor drugs) VTE rate of 1.0%.

The sample size calculation is for a superiority comparison based on symptomatic VTE (DVT or PE) at 90 days at 90% power with a significance level of 5%, assuming 1.0% in the no stocking (control) and 0.5% in the stocking (active) groups.

Assuming an intraclass correlation coefficient (ICC) on the VTE at 90 days outcome of 0.001 (consistent with the control outcome rate varying uniformly between 0.5% and 1.5%)^18^ and a coefficient of variation of site size of 0.25 (consistent with sites varying according to a normal distribution mean=350 and SD=88, ie 95% of the sites would be between 174 and 526 participants), with 25 sites randomised to active and 25 sites to control, the study would need to recruit 17 500 patients. Allowing for 15% loss to follow, but no sites lost to follow-up, and adjusting for the group sequential design with one formal interim analysis at 50% with 90-day follow-up, 21 472 participants are required. We do not believe there will be any meaningful crossover. A check on the sample size assumptions will be incorporated when there are 10 sites across both arms that have recruited at least 100 patients each (checking on variability in the control outcome for ICC and checking zero crossover). At this stage, as well as confirming the overall maximum sample size, the schedule for a single efficacy or futility analysis at around 50% of the target recruitment with mature 90-day follow-up will be included.

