### Patient and public involvement

During the grant application stage, online surveys were launched to learn public views on the PETS study. These surveys helped to inform important aspects of the trial, including the number of visits and questionnaires used in the study. Two patient advisors, both with lived experience of VTE, have been involved in the design of the study and review of patient-facing materials. Both were grant coapplicants, have agreed to sit on the TSC, facilitate patient advisory groups, will assist with the dissemination of results and are coauthors of this manuscript.

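### The month-13 pilot review confirms or changes the sample size from by-arm VTE rates labelled blinded, when only about two to four mature events are expected

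*Protocol article*

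**What the plan says.** Under Internal pilot, recruitment for the pilot runs from the "beginning of month 7 to end of month 12 of the overall study timeline". The review follows one month later: "The TSC will meet at the end of month 13 (allowing 1 month of processing time after the 6 months of recruitment"). The TSC meets "with blinded estimation of the rate of VTE for each arm. This will confirm the sample size or lead to a sample size re-estimation".

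The sample size section rests on two VTE rates, "assuming 1.0% in the no stocking (control) and 0.5% in the stocking (active) groups", at 90 days. It describes another check on the assumptions, triggered when 10 sites have each recruited at least 100 patients. That check covers variability of the control outcome (for the ICC) and crossover, and it also serves to confirm the maximum sample size. The only formal interim analysis is placed at about 50% of mature 90-day data.

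Under Data monitoring, safety and quality control, the iDMC monitors the main outcome measures, including efficacy, and the TSC has overall supervision.

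**The concern.** There are three problems with the step as written.

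- **The quantity.** A blinded estimate of an event rate is pooled over arms. A rate for each arm is comparative. If the intention is masked labels (A and B), the reader of the report still sees how far apart the arms are and lacks only the direction.
- **The maturity of the data.** The outcome needs 90 days, and the review takes place one month after pilot recruitment ends. Anyone recruited in the last two pilot months cannot have a complete outcome by then.
- **The recipient.** The plain reading is that the TSC receives these rates, whereas the protocol gives efficacy monitoring to the iDMC.

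At stake is a change to the size of a 21 472-participant trial made on a handful of events, and an early disclosure that cannot be reversed.

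**Working it through.** **Inputs.** From Internal pilot: four sites opened per month, 20 participants per centre-month, a pilot target of 1440, recruitment in months 7 to 12, review at the end of month 13. From Sample size and study duration: 1.0% and 0.5%, 15% loss, 90% power, 5% significance (taken as two-sided; the text does not say), ICC 0.001, mean site size 350 with coefficient of variation 0.25, 25 + 25 sites. From Primary outcome and Follow-up periods: a 90-day window.

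**1. Reproduce the pilot target.** With sites opening steadily at 4 per month, 4t sites are open after t months, and the number recruited is 20 × 4 × t²/2 = 40t². At t = 6 this is 40 × 36 = 1440, the plan's figure.

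**2. Participants past day 90.** Ninety days is 2.957 months.
- Data cut at the end of month 12: 40 × (6 − 2.957)² = 370.
- Data cut at the end of month 13: 40 × (7 − 2.957)² = 654.
- Using whole months (recruited by the end of month 10, t = 4): 40 × 16 = 640.

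**3. Expected events.** The pooled rate at 1:1 is (1.0% + 0.5%)/2 = 0.75%.
- 370 × 0.85 × 0.0075 = 2.4.
- 654 × 0.85 × 0.0075 = 4.2.
- 640 × 0.85 = 544 outcomes, × 0.0075 = 4.1 events: 272 × 1.0% = 2.7 control and 272 × 0.5% = 1.4 stocking.
- All 1440 mature, which month 13 does not allow: 1440 × 0.0075 = 10.8 without loss, 9.2 after 15% loss.
- Full trial, for scale: 17 500 × 0.0075 = 131.

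**4. Precision.** Exact (Clopper–Pearson) 95% intervals, ignoring clustering:
- pooled, 4/544 = 0.74%: 0.20% to 1.87%;
- control arm, 3/272 = 1.1%: 0.23% to 3.2%;
- pooled, 11/1440: 0.38% to 1.36%.

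**5. What the review would see if the plan's assumptions were exactly true** (binomial, 272 per arm, 1.0% against 0.5%):
- at most one control event (observed rate ≤ 0.37%): probability 0.24;
- five or more control events (≥ 1.8%): probability 0.14;
- no stocking event: probability 0.26;
- observed control rate no higher than the stocking rate: probability 0.34.

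**6. What this means for sample size.** The standard two-proportion formula at 1.0% against 0.5% gives 6256 per arm. The design effect is 1 + ((0.25² + 1) × 350 − 1) × 0.001 = 1.371. The total is 2 × 6256 × 1.371 ≈ 17 152, or 24.5 sites of 350 per arm. Rounding up to 25 gives 25 × 350 × 2 = 17 500, as stated. Keeping a halving of risk and the same design effect, a control rate of 0.5% needs about 34 400 and a rate of 2.0% about 8 500, before loss. Both rates lie inside the control-arm interval in step 4.

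**7. Timing of the other check.** At 20 per month a site needs 5 months to reach 100. The tenth site opens 10/4 = 2.5 months into recruitment and reaches 100 at 7.5 months, the middle of month 14. The 10-site check therefore falls about half a month after the month-13 meeting and uses different quantities.

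**The case against.** The strongest replies are these.

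- **The wording may be loose.** The authors may have meant a pooled rate, or a check of the control rate alone, and the full protocol may say so. That is possible, but the article names a rate for each arm as the input to the decision. It needs correcting whatever was meant.
- **The TSC is independent.** The Statistical analysis and Data monitoring sections both say so. A reader might infer from "Both were grant coapplicants, have agreed to sit on the TSC" that people running the trial would see its interim results. The documents do not support that: the two members are patient advisors, the coauthorship stated is of the protocol article, and day-to-day progress belongs to the trial manager and Trial Management Group. Nor does the text say that the iDMC is bypassed. What stands is narrower: by-arm outcome rates go to a body other than the one charged with monitoring efficacy.
- **Type I error.** A reader might infer an unblinded re-estimation without error control. No resizing rule is given and nothing says that the observed difference drives the size, so this cannot be established. About 4 of 131 expected events is about 3% of the information, so any inflation is probably small. The same sparseness limits how much the rates reveal about the true effect.
- **Early events count.** VTE is also collected at day 7, so participants short of day 90 may add events. That raises the count above four, but to no more than about 11, and precision remains poor.

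**Conclusion.** The point holds as a defect in what the article fixes. The step calls a by-arm rate blinded, puts it to the TSC and lets it decide the sample size, when about 2 to 4 mature events are expected. The pooled interval of 0.20% to 1.87% spans roughly a ninefold range (1.87/0.20 = 9.4). Even the unattainable case of 1440 mature participants leaves 0.38% to 1.36%.

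The event count is derived, not stated. It assumes the target pace, steady site opening (which reproduces 1440), 15% loss and the plan's own rates. Other site-opening, loss and cut-off assumptions give about 2 to 6 mature events, with the same conclusion. Clustering, ignored here, would widen the intervals.

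The main harms are a decision driven by noise and disclosure of by-arm results outside the iDMC. The stronger readings, that the type I error is materially inflated or that the trial team would see the results, are not supported. Without a stated rule the inflation cannot be quantified.

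**What to change.** - Limit the month-13 review to recruitment, site set-up, crossover and follow-up completeness. Delete the by-arm VTE rates and the re-estimation from it.
- If the sample size is to be re-estimated, base this on the VTE rate pooled over both arms, once a prespecified number of mature 90-day outcomes or events is reached.
- Keep by-arm rates to the iDMC.
- Reconcile this with the 10-site check in the sample size section, so that one check, with one trigger and one set of inputs, confirms the sample size.

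This changes only wording, in the protocol and in any committee charters. It needs no extra participants or data. The cost is timing: a resizing decision would come later and leave less time to add sites.
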